#### Termination criteria

2.3.4

(1) Voluntary withdrawal or loss to follow-up by the patient;(2) Inability to continue participation due to serious adverse events;(3) Failure to comply with the study plan to complete the scheduled medication treatment and follow-up arrangements:
1) Investigational drug: For medication adherence assessment in chronic disease studies, the internationally accepted standard is between 80 and 120%. In this study, follow-up visits are conducted every 3 months. Using an illustrative example, the actual number of pills taken (A) is calculated by subtracting the number of pills returned at the visit from the number previously dispensed. The expected pill count is 90 × 2 × 3 = 540pills, yielding an acceptable adherence range of 80% × 540–120% × 540, i.e., rounded to 432–648 pills. If A falls outside this range, the patient is considered non-adherent and will be regarded as a dropout.2) Chemotherapy: According to the CSCO guidelines, postoperative adjuvant chemotherapy for stage IIIB, IIIC colorectal cancer should last 4–6 months. Therefore, patients who are intolerant to chemotherapy and receive it for ≤ 3 months will be regarded as dropouts, as this may increase the risk of recurrence and metastasis.

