**Figure 2 F2:**
[figure not shown]
NCI-CTCAE Diarrhea Grading Scale. This table is based on the National Cancer Institute's (https://dctd.cancer.gov/research/ctep-trials/for-sites/adverse-events) Common Terminology Criteria for Adverse Events (NCI-CTCAE v5.0) (36), the standard classification used in oncology . ADL, activities of daily living. Definition: A disorder characterized by an increase in frequency and/or loose or watery bowel movements. ^a^Instrumental ADL refers to preparing meals, shopping for groceries or clothes, using the telephone, managing money, etc. ^b^Self-care ADL refers to bathing, dressing and undressing, feeding self, using the toilet, taking medications, and not bedridden.

Meanwhile, due to factors such as chemotherapy, subjects may experience grade 2 or higher diarrhea during the study period, so we need to be highly cautious and develop effective treatment plans in advance. When grade 2 or higher diarrhea occurs, emergency medications such as smectite powder, loperamide, or octreotide, should be administered after evaluation by physician. The investigator must record in the CRF detailed information, including the diarrhea grade, name of the rescue medication, dosage, and time of administration. If the patient experiencing Grade 3 diarrhea, the investigational drug will be temporarily discontinued until the toxicity resolves to Grade 1 or baseline, upon which it may be resumed. In addition, once a patient experiencing Grade 4 diarrhea, the investigational drug must be permanently discontinued and the subject discontinue the study.

During the follow-up period, regular assessments of tumor status will be performed, along with routine laboratory examinations including complete blood count, biochemical tests, and routine stool tests, as well as imaging examinations consisting of chest-abdomen-pelvis CT or contrast-enhanced abdomen-pelvis CT/MRI. For each quarterly follow-up visit, a window period of ±7 days is permitted. If a patient is unable to attend the hospital visit, conduct a telephone follow-up and remind the patient to complete the routine check-up. At the end of the 1-year follow-up period, a standard colonoscopy will be performed again, and blood and fecal samples will be collected.

In addition, if disease recurrence or metastasis occurs in the patient during treatment and follow-up, sample collection shall be performed at the time of recurrence and metastasis.

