### Statistical analysis

2.9

First, normality tests were performed on the measurement data. For data conforming to a normal distribution, parametric statistical methods including *t*-test, paired *t*-test, analysis of variance, and analysis of covariance were used. For non-normally distributed data, nonparametric methods such as rank-sum test and paired rank-sum test were adopted. Enumeration data were analyzed using chi-square test and Fisher's exact test, while ordinal data were analyzed using Ridit analysis, CMH test, or other nonparametric methods. In the multicenter comprehensive efficacy analysis, the CMH test was used for enumeration data, and analysis of covariance was used for measurement data. All statistical analyses were performed using SAS 9.3 software. For patients with missing data due to dropout or loss to follow-up, the last observation carried forward method may be used for imputation, followed by a sensitivity analysis of the results. All statistical tests were two-sided, and P < 0.05 was considered statistically significant.

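### The pill-count dropout rule counts protocol-ordered drug holds as missed doses, so an otherwise fully adherent patient held for 19 or more days in a 90-day interval becomes a dropout

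*Protocol article*

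**What the plan says.** Two rules in the protocol article bear on the same patient.

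**Section 2.3.4 (Termination criteria).** The parent item is "Failure to comply with the study plan to complete the scheduled medication treatment and follow-up arrangements". Under it, pills taken (A) are "calculated by subtracting the number of pills returned at the visit from the number previously dispensed". The benchmark is full dosing: "The expected pill count is 90 × 2 × 3 = 540pills". The accepted band is "80% × 540–120% × 540, i.e., rounded to 432–648 pills". The consequence carries no exception: "If A falls outside this range, the patient is considered non-adherent and will be regarded as a dropout".

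**Section 2.7.3 (Follow-up program, text after Figure 2).** At Grade 3 diarrhoea, "the investigational drug will be temporarily discontinued until the toxicity resolves to Grade 1 or baseline, upon which it may be resumed". No maximum hold is given. Permanent discontinuation and leaving the study are named only for Grade 4.

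Two further statements matter for the consequences. Section 2.7.3 also says: "For each quarterly follow-up visit, a window period of ±7 days is permitted". Section 2.9 says: "For patients with missing data due to dropout or loss to follow-up, the last observation carried forward method may be used for imputation".

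**The concern.** A is measured against what a patient would take with no interruption. Pills withheld on the protocol's own instruction come back at the visit and are counted as pills the patient failed to take. With a long hold, or several shorter ones in the same interval, a patient who followed section 2.7.3 exactly falls below 432 and is labelled non-adherent and a dropout under section 2.3.4. That is at odds with the parent criterion, which concerns failure to follow the study plan. It is also at odds with the grading in section 2.7.3, which ties leaving the study to Grade 4 and not to Grade 3.

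What is at stake is the status of randomised patients. The protocol foresees diarrhoea of Grade 2 or higher during chemotherapy, which all patients receive, so holds are an expected event. If the dropout label ended outcome assessment, DFS data would be missing and the last-observation-carried-forward option in section 2.9 could come into play. Section 2.3.4 does not say whether follow-up continues after the label, so this last step is a possibility only.

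**Working it through.** **Inputs.** Dose: 3 units of 0.1 g twice daily, so 6 pills a day (sections 2.2 and 2.6). Interval: 90 days (the pill count in section 2.3.4). Accepted band: 80% to 120% of expected (section 2.3.4). Hold: all doses stopped, with no stated maximum (section 2.7.3).

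**The plan's own figures.** Expected = 90 × 2 × 3 = 540. Limits = 0.8 × 540 = 432 and 1.2 × 540 = 648. Both reproduce exactly.

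**Held days, every permitted dose taken.** With h full held days, A = 540 − 6h. The patient fails when 540 − 6h < 432, that is h > 18.

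| Held days in 90 | A | Share of 540 | Result |
|---|---|---|---|
| 14 | 456 | 84.4% | passes |
| 18 | 432 | 80.0% | passes |
| 19 | 426 | 78.9% | dropout |
| 21 | 414 | 76.7% | dropout |

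**Held days combined with some missed doses.** If the patient takes a share a of the permitted doses, A = a × 6 × (90 − h).

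| On-drug adherence | Last pass | First fail |
|---|---|---|
| 95% | h = 14: 76 × 5.7 = 433.2 | h = 15: 75 × 5.7 = 427.5 |
| 90% | h = 10: 80 × 5.4 = 432.0 | h = 11: 79 × 5.4 = 426.6 |
| 85% | h = 5: 85 × 5.1 = 433.5 | h = 6: 84 × 5.1 = 428.4 |

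**Sensitivity to interval length.** The ±7-day window is stated in the paragraph on the follow-up period; I assume here that it also covers treatment visits.

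- *Limit fixed at 432.* Seventy-one dosing days give 426 and fail, so failure starts at (interval − 71) held days. With one visit shifted this is 83 − 71 = 12 or 97 − 71 = 26. With both visits shifted it is 76 − 71 = 5 or 104 − 71 = 33.
- *Expected count follows the actual interval.* For 83 days the limit is 0.8 × 498 = 398.4, and 66 dosing days give 396, so failure starts at 17 held days. For 97 days the limit is 0.8 × 582 = 465.6, and 77 dosing days give 462, so failure starts at 20. Held days still count against the patient.

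**With hold days removed from the expected count.** Expected = 6 × (90 − h).

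- 19 held, all other doses taken: expected 426, band 340.8 to 511.2, taken 426 = 100%.
- 15 held at 95%: expected 450, band 360 to 540, taken 427.5 = 95%.
- 11 held at 90%: expected 474, band 379.2 to 568.8, taken 426.6 = 90%.

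All three would be dropouts under the rule as written, and all three pass once the hold is allowed for.

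**The case against.** There are four serious replies.

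*The count is only an illustration.* Section 2.3.4 introduces the calculation as an example, and its parent criterion is non-compliance, which a required hold is not. A sensible reader could apply the rule with that in mind. This partly stands: the intent is probably benign. But the sentence with the consequence applies that same band directly, and the article gives no other operating rule.

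*This is drug-accountability detail for the full protocol.* It may be handled there. The point, however, is not that detail is absent. The article states both rules, and applied together they misclassify a compliant patient.

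*The rule may be a deliberate exposure threshold.* The next item in section 2.3.4 treats patients who cannot tolerate chemotherapy and receive it for three months or less as dropouts, and they are not at fault either. On that view, anyone below 80% of the study drug should be treated alike, and the correction has a price: a patient held for 45 of 90 days could score 100%. The price is real. But the rule calls the patient non-adherent, under a heading about failing to follow the plan, and that does not fit a pure exposure threshold.

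*It is rare and without shown effect.* This stands in part. Section 2.7.3 directs rescue medication from Grade 2, a total of 19 full days is long, and section 2.9 ties no analysis population to the pill count. Some of the lower thresholds also include genuinely missed doses. Frequency and effect on the result are unknown, which limits the point to a minor one.

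**Conclusion.** The concern holds as a minor inconsistency. For a 90-day interval, full held days and otherwise perfect intake, the boundary is exact: 18 held days pass and 19 fail. It falls to 15, 11 or 6 days at 95%, 90% or 85% adherence on the remaining days, and it moves with the visit interval under the window assumption. The share of patients affected cannot be estimated, since the article reports neither the incidence nor the duration of Grade 3 diarrhoea. No bias in the DFS comparison is shown. Any such effect would require the label to end outcome follow-up, which the article neither states nor excludes. Restarting after a hold is optional, and section 2.7.3 does not expressly require a Grade 3 patient to be retained, so the clear conflict is confined to patients whose drug is held and then resumed.

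**What to change.** In section 2.3.4:

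1. Define expected pills as 6 × (actual days between dispensing and return − days of protocol-required hold), and apply the 80–120% band to that figure.
2. Add one sentence: a patient whose drug was held and resumed under section 2.7.3 is not a dropout because of the held days and remains in DFS follow-up.
3. Report total dose taken as a separate exposure measure. In the 19-day example this is still 78.9% of full dosing, so low exposure stays visible.

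The cost is one formula, one sentence and recording of hold start and stop dates. No visit or procedure is added. The drawback is that some patients with low total exposure will count as adherent, which the separate exposure figure is there to show.

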### Sample size

2.4

This is a RCT with the BBR group as the intervention group and the placebo group as the control group. The 2-year DFS rate in postoperative CRC patients was set as the primary endpoint. According to our previous small-sample observations and literature review, the 2-year DFS rate was estimated to be 67% in the control group and 77% in the intervention group (4). A 1:1 parallel-group design was adopted, with a two-sided type I error α = 0.05 and a test power (1–β) = 0.8. Sample size calculation was performed using PASS 2021 software, yielding a required sample size of 316 patients in the intervention group and 316 patients in the control group. Considering a 15% dropout rate due to loss to follow-up and refusal, at least 363 patients were needed in each group, resulting in a total target sample size of 726 patients.

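### The 15% dropout allowance covers only loss to follow-up and refusal, while the termination criteria create further dropouts with no stated rate; 80% power depends on whether those patients stay in follow-up and in the primary analysis

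*Protocol article*

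**What the plan says.** Section 2.4 (Sample size) rests on these assumptions: "the 2-year DFS rate was estimated to be 67% in the control group and 77% in the intervention group". The error rates are: "A 1:1 parallel-group design was adopted, with a two-sided type I error α = 0.05 and a test power (1–β) = 0.8". The result is given as "yielding a required sample size of 316 patients in the intervention group and 316 patients in the control group". The allowance is then added with its two causes named: "Considering a 15% dropout rate due to loss to follow-up and refusal, at least 363 patients were needed in each group". Doubling the figure per arm gives the overall target of 726.

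Section 2.3.4 (Termination criteria) adds other routes to dropout. On the three-monthly pill count, with an accepted range of 432 to 648, it says: "If A falls outside this range, the patient is considered non-adherent and will be regarded as a dropout". On chemotherapy: "patients who are intolerant to chemotherapy and receive it for ≤ 3 months will be regarded as dropouts". It also lists being unable to continue because of a serious adverse event, without using the word dropout there.

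Section 2.7.3 (Follow-up program) says of a patient with grade 4 diarrhoea: "the investigational drug must be permanently discontinued and the subject discontinue the study".

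Section 2.9 (Statistical analysis) is the only place that says how dropouts are analysed. Missing data from dropout or loss to follow-up may be imputed by LOCF, and a sensitivity analysis follows. It does not say that dropouts are removed from the primary analysis, and it does not firmly say that they are kept.

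**The concern.** The sample size and the termination rule count different sets of patients. A patient who fails a pill count, or who cannot tolerate chemotherapy beyond 3 months, is neither lost to follow-up nor a refusal, yet section 2.3.4 makes that patient a dropout. The same gap applies to terminations for serious adverse events and for grade 4 diarrhoea.

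These groups may not be negligible. The pill count is checked every 3 months over a 12-month treatment period, so failures can accumulate. Study drug is taken alongside adjuvant chemotherapy, and the protocol itself plans for diarrhoea and for drug interruption.

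If these patients stop contributing DFS data, or are left out of the primary analysis, the trial has less information than section 2.4 implies. A null result would then be read against a power that the trial did not have.

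**Working it through.** **Inputs.** From section 2.4: 67% against 77%, two-sided 0.05, power 0.80, 1:1 allocation, 316 per arm before and 363 per arm after the allowance, and a 15% loss. From section 2.3.4: a pill-count check every 3 months, so four checks in the 12 months of treatment. Every rate for the additional dropout causes below is an assumption, because the article gives none.

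**Reproducing the plan.** For two proportions with pooled variance under the null and mean rate 0.72:

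n = [1.960·√(2·0.72·0.28) + 0.842·√(0.67·0.33 + 0.77·0.23)]² / 0.10² = 315.3, rounded up to 316 per arm.

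This matches the protocol. Power at 316 is 80.1%. The 363 is 316 × 1.15 = 363.4, rounded down.

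**Room left by the allowance.** 363 × 0.85 = 308.6 per arm, power 79.1%. A total loss of 13% leaves 315.8 and 80.1%. So the allowance just about covers a 15% loss from all causes and leaves no reserve. About 1 point of every shortfall below (80.1% to 79.1%) comes from multiplying by 1.15 instead of dividing by 0.85. That is a separate matter.

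**If the additional dropouts are excluded.** Evaluable n = 363 × 0.85 × (1 − e), where e is the assumed share of the remaining patients lost to the unbudgeted causes:

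| e | n per arm | total loss | power |
|---|---|---|---|
| 0% | 309 | 15.0% | 79.1% |
| 5% | 293 | 19.3% | 77.1% |
| 10% | 278 | 23.5% | 74.8% |
| 20% | 247 | 32.0% | 69.8% |

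**How quickly the pill-count rule could accumulate.** If failures are independent across quarters, the share failing at least once is 1 − (1 − q)⁴: 7.8% for q = 2% and 18.5% for q = 5%. If the same patients fail repeatedly, q = 2% could mean as few as 2% of patients, so 7.8% is the upper end for that rate.

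**If dropouts are kept and imputed by LOCF.** As an extreme case, suppose every dropout leaves before any event and is carried forward as disease-free. With total loss L, each arm's rate becomes p(1 − L) + L, and all 363 per arm are analysed:

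- L = 15%: 72.0% against 80.5%, power 76.8%.
- L = 23.5% (e = 10%): 74.8% against 82.4%, power 71.0%.
- L = 32% (e = 20%): 77.6% against 84.4%, power 64.6%.

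Some events would precede dropout, so these figures are a bound.

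**If all 363 per arm are followed for DFS and analysed.** Power is 85.2% at the planned rates. If an assumed 5%, 10% or 15% of berberine patients have only the control rate, the berberine rate is 76.5%, 76.0% or 75.5% and power is 81.3%, 76.7% or 71.7%.

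**The case against.** A reader might infer that the 80% power is simply not delivered. The article does not support that. Section 2.3.4 labels these patients dropouts and stops there. Section 2.9 points towards imputation, which would retain them. The definition of the analysis set is commonly left to a statistical analysis plan, and none is shown here. With every randomised patient followed and analysed at the planned rates, power would be above 80%.

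It is also fair that every additional rate is assumed, and that the causes overlap. A patient who refuses or is lost may also fail a pill count or stop chemotherapy, so adding the causes as if independent overstates the total. If the 15% was meant to cover all causes, power is 79.1%, which is close enough to the target.

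Two things remain. First, the mismatch is between printed statements: section 2.4 names the causes that it budgets for, and section 2.3.4 names others. A later analysis plan would not change what the allowance was said to cover. Second, imputation is optional in section 2.9 and does not by itself protect power. Carrying a patient forward as disease-free can shrink the difference between arms, as the bound above shows. Power is protected by continued DFS follow-up, and a heading of termination criteria points away from that.

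**Conclusion.** The point holds as an inconsistency with a conditional effect on power. The 15% in section 2.4 does not cover the dropouts that section 2.3.4 creates or the study discontinuations in sections 2.3.4 and 2.7.3, and the article gives no rate for them.

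The stated 80% holds only if these patients stay in follow-up and in the primary analysis, or if total loss from all causes stays near 15%. If they are excluded, power is about 77%, 75% or 70% for an assumed further loss of 5%, 10% or 20% of the remaining patients. No single corrected figure can be given.

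These results assume 363 per arm, rates of 67% and 77%, and the pooled two-proportion test that reproduces 316. They take the section 2.4 target as given; the smaller total in the abstract is a different question.

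**What to change.** Reconcile sections 2.3.4, 2.4, 2.7.3 and 2.9 so that dropout has one meaning.

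- **Preferred.** Keep the word for loss to follow-up and withdrawal, which matches the 15%. Record pill-count failure and short chemotherapy as protocol deviations or treatment discontinuation, continue DFS follow-up, and keep these patients in the primary analysis as randomised. Note in section 2.4 that non-adherence may still dilute the effect; retaining these patients does not guarantee 80%.
- **Otherwise.** State in section 2.4 the expected total loss from all listed causes and restate the power at 363 per arm, for example about 75% if a further 10% of the remaining patients are lost.
- **Grade 4 diarrhoea and serious adverse events.** State only whether DFS data are still collected and analysed after the patient stops, and make the passages agree. The clinical rule itself is not in question here.

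The cost is wording in four sections. The preferred route adds DFS follow-up for any patient who would otherwise have been terminated. The alternative needs no more patients, provided that the sponsor accepts the lower stated power.

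### The 15% dropout allowance was added as 316 × 1.15 rather than 316 / 0.85, so 726 patients fall slightly short of the 632 evaluable that the plan requires

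*Protocol article*

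**What the plan says.** Section 2.4 (Sample size) sizes the trial on a comparison of two proportions. The endpoint is fixed first: "The 2-year DFS rate in postoperative CRC patients was set as the primary endpoint". The planning rates follow: "the 2-year DFS rate was estimated to be 67% in the control group and 77% in the intervention group". The test settings are "two-sided type I error α = 0.05" and "test power (1–β) = 0.8", with equal allocation. The software result is reported as "yielding a required sample size of 316 patients in the intervention group and 316 patients in the control group".

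The dropout step is then given in one sentence: "Considering a 15% dropout rate due to loss to follow-up and refusal, at least 363 patients were needed in each group". Doubling this gives the overall target of 726. The section does not print the formula that takes 316 to 363.

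**The concern.** A dropout rate is a share of the patients who are enrolled. To have 316 left after 15% are lost, the number enrolled must satisfy N × 0.85 ≥ 316, so 316 is divided by 0.85. Multiplying by 1.15 adds 15% of the evaluable number instead, which is always too few. The stated 363 looks like the second calculation.

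At stake is whether the stated target gives the stated power at the stated dropout. The requirement of 316 carries almost no reserve (its power is 80.1%), so any under-inflation takes the design below 80%.

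**Working it through.** **Inputs, all from section 2.4:** control rate p1 = 0.67; intervention rate p2 = 0.77; difference d = 0.10; two-sided α = 0.05 (z = 1.960); power 0.80 (z = 0.842); 1:1 allocation; 316 per arm before dropout; dropout 15%; 363 per arm and 726 in total after dropout.

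**Step 1. Reproduce 316.** Two-proportion test with pooled variance under the null and no continuity correction; mean rate p̄ = 0.72:

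n = [1.960 × √(2 × 0.72 × 0.28) + 0.842 × √(0.67 × 0.33 + 0.77 × 0.23)]² / 0.10²

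= [1.960 × √0.4032 + 0.842 × √0.3982]² / 0.01 = 315.3, rounded up to **316 per arm**.

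This matches the plan, so the base figure is not in question.

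**Step 2. Identify the inflation used.**

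| Rule | Result per arm | Agrees with 363? |
|---|---|---|
| 316 × 1.15 | 363.4 | yes, rounded down |
| 316 / 0.85 | 371.8, so 372 | no |

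Rounding 363.4 down also sits badly with a figure described as a minimum; rounded up it is 364.

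**Step 3. Apply the plan's dropout rate to the plan's target.**

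- Per arm: 363 × 0.85 = 308.55, against 316 required.
- In total: 726 × 0.85 = 617.1, against 632 required, about 15 short.
- Dropout that 363 can absorb: 1 − 316/363 = 0.129, or **12.9%**.

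**Step 4. Power with the patients who remain.** With the same test,

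power = Φ{[d√n − 1.960 × √0.4032] / √0.3982}

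| n per arm analysed | Power |
|---|---|
| 316 (the plan's requirement) | 80.1% |
| 308.55 (363 less 15%) | 79.1% |
| 363 (no loss at all) | 85.2% |

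**Step 5. Size of the correction.** 372 − 363 = 9 per arm; 744 − 726 = 18 in total; 18/726 = 2.5%.

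**Step 6. Does the choice of test formula rescue 363?** The unpooled-variance formula gives 312.5, so 313 per arm or 626 in total. The 617 who remain are still too few. With a continuity correction the requirement rises to 335 per arm, and the gap widens.

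**The case against.** The arithmetic itself is hard to contest, but there are fair points on how much weight it should carry.

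- **It is small.** One point of power is less than the uncertainty in the inputs. The 67% and 77% rest partly on the team's own small-sample observations, and the 15% is a round number. Moving from the unpooled to the continuity-corrected formula shifts the requirement from 313 to 335 per arm, more than the 9 at issue. This stands, and it limits the point to a minor correction.
- **The method is inferred.** Section 2.4 prints no inflation formula. That is true, but 363 agrees with multiplication and not with division. Whatever the route, 363 less 15% is below 316.
- **Dropouts might not be lost to the analysis.** Section 2.9 says that last observation carried forward may be used for missing data, and a patient who leaves after a recurrence has already contributed an event. So 79.1% is conditional on dropouts leaving the primary analysis. This stands as a condition on the power figure. It does not justify 363: section 2.9 only permits the imputation, and inflating for dropout makes sense only if those patients are treated as lost. Carrying patients forward as disease-free could also dilute the difference between arms.
- **The 15% may itself be incomplete.** Section 2.4 attributes it to loss to follow-up and refusal. Section 2.3.4 also counts as dropouts patients outside the pill-count range and those intolerant to chemotherapy who receive it for three months or less. The documents give no rate for these, so 744 is right for 15% but not necessarily for the true loss. That is a reason to review the rate, not to leave the arithmetic as it is.
- **A larger conflict exists.** The abstract gives a total of 306, not 726. That is a separate matter and more serious: with 153 per arm and no loss, power is about 49.5%. It should be settled first, but it does not make 363 correct.

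**Conclusion.** The dropout step is wrong as printed. On the plan's own inputs, 363 per arm does not leave 316 after a 15% loss; it leaves 308.55. The figure that does is 372 per arm, 744 in total. The shortfall is 9 per arm, 18 overall (2.5%), and power is 79.1% rather than at least 80%.

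The 79.1% assumes that the planned rates hold, that the loss is 15% in each arm, and that dropouts leave the primary analysis. The inflation error itself depends on none of these except the 15%, which is the plan's own figure. This is a minor correction to a planning number, not evidence of a seriously underpowered design.

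**What to change.** Change one line in section 2.4, in either of two ways:

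- **Correct the target:** state that 316 / 0.85 = 371.8, so 372 patients per group and 744 in total. This costs 18 more patients.
- **Keep 726 and describe it accurately:** state that 363 per group allows for 12.9% dropout at the planned power, or that it gives about 79% power if 15% of patients drop out and are not analysed. This costs nothing and adds no patients.

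In either case, print the inflation formula. Make the edit together with the reconciliation of 726 with the abstract's 306, so that the error is not carried into whichever total is confirmed.
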